## Abstract

Cognitive reappraisal (CR) is one of the core treatment components of cognitive behavioral therapy (CBT) and is the gold standard treatment for major depressive disorders. Accumulating evidence indicates that cognitive reappraisal could function as a protective factor of cognitive vulnerability to depression. However, the neural mechanism by which CR training reduces cognitive vulnerability to depression is unclear. There is ample evidence that the prefrontal–amygdala circuit is involved in CR. This study proposes a novel cognitive bias model of CR training which hypothesizes that CR training may improve the generation ability of CR with altered prefrontal–amygdala functional activation/connectivity, thus reducing negative cognitive bias (negative attention bias, negative memory bias, negative interpretation bias, and/or negative rumination bias) and alleviating depressive symptoms. This study aims to (1) explore whether there is abnormal CR strategy generation ability in individuals who are cognitively vulnerable to depression; (2) test the hypothesis that CR training alleviates depressive symptoms through the mediators of cognitive bias (interpretation bias and/or rumination bias); (3) explore the neural mechanism by which CR training may enhance the ability of CR strategy generation; and (4) examine the short- and long-term effects of CR training on the reduction in depressive symptoms in individuals who are cognitively vulnerable to depression following intervention and 6 months later. The study is promising, providing theoretical and practical evidence for the early intervention of depression-vulnerable individuals.

## Introduction

Depressive disorder is an affective mental disorder with depressive mood and anhedonia as the defining symptoms. It may cause functional disability, seriously affect social functioning and quality of life, and create a heavy socioeconomic burden. The disease burden of depressive disorders accounts for 10.3% of the total disease burden (Smith, 2014), which is estimated to be the cause of the world’s top disease burden in 2030. Therefore, early identification and intervention to reduce disease burden is currently the focus of research on depressive disorders.

According to the cognitive vulnerability–stress theory of depression, cognitive vulnerability can interact with stress to increase the likelihood of depression (Abramson et al., 1989, 1999). Cognitive vulnerability manifests as negative cognitive biases, such as biases in attention, interpretation, and rumination (Dai and Feng, 2008; Chen and Feng, 2015; Zhang and Feng, 2016; Yan et al., 2017). The combined cognitive bias hypothesis in depression proposed that negative attention bias can lead to interpretation bias, which in turn induces rumination and subsequently more depressive symptoms. This hypothesis is supported empirically by path analyses of these variables (attention bias→interpretation bias→rumination→depressive symptoms; Everaert et al., 2012, 2017).

Cognitive reappraisal (CR), which changes the affective regulation process of emotional responses through the reinterpretation of the meaning of emotional stimuli, represents a core technique of cognitive behavioral treatment (CBT), the gold standard psychotherapy of depressive disorder (Shore et al., 2017). Typically, depressed individuals manifest deficits in the habitual use of CR strategies. Compared with other emotion regulation strategies (e.g., emotion expression suppression), deficits in positive CR (the frequency with which individuals interpret stressful life events as positive rather than threatening) are specific factors that can predict depressive symptoms (Garnefski et al., 2005) and positive emotions initially and depression and anxiety symptoms 3–6 months later (Nowlan et al., 2016). In contrast, frequent use of CR may have beneficial effects that protect individuals from depression vulnerability. Frequent use of CR can modify an individual’s interpretation bias, dampen rumination bias, and thus alleviate depression symptoms (attention bias→interpretation bias→CR→rumination→depressive symptoms) (Everaert et al., 2017). CR frequency mediated the relationship between interpretation biases and depressive symptoms in individuals at high familial risk for depression and alleviated the negative impact of interpretation bias on depressive symptoms (interpretation bias→CR→depressive symptoms) (Sfärlea et al., 2021). Depression-resilient individuals tend to use CR to assign a new emotional meaning to stressful events (Knyazev et al., 2017), whereas adolescents with parents having a history of depression (depression-vulnerable individuals) who frequently use CR as an emotion regulation strategy will experience less depression and have higher positive emotions (Kudinova et al., 2018). Specifically, CR was positively linked with the ability to inhibit negative content during a negative affective priming task in individuals with low rumination (Daches and Mor, 2015). Individuals who frequently use CR can better inhibit the interference of distracting negative stimuli (Cohen et al., 2012) and have fewer depressive symptoms in response to unpredictable stress (Troy et al., 2013). The ability to generate a non-negative CR predicts fewer stress responses (lower cortisol levels) when faced with depression-related acute stress (Tsumura et al., 2015). Therefore, the CR ability may have a positive impact on reducing depressive symptoms through inhibition or compensation of negative cognitive bias (e.g., interpretation bias and/or rumination bias) as well as through reduction of physiological arousal.

Notably, previous studies utilizing self-report measures, such as the Emotion Regulation Questionnaire (ERQ) (Gross and John, 2003) and Cognitive Emotion Regulation Questionnaire (CERQ), mainly measure an individual’s tendency, such as frequency (trait) and extent (state), to use CR strategies specified by the developers of the questionnaire in daily life. However, CR tendency reflects typical behavioral patterns rather than capacity for best performance (e.g., CR ability) (Perchtold et al., 2017). Furthermore, self-reported CR tendency is moderately correlated with personality factors such as self-acceptance and environmental mastery (*r* = 0.35 and 0.41) (Gross and John, 2003), which may influence the motivation to use CR strategies and cannot objectively quantify the ability of the individual to generate a CR strategy. In contrast, CR ability, which is also termed reappraisal effectiveness (RE), can be experimentally measured by changes in spontaneous emotion responses after the individual is required to adopt a CR strategy compared to passively viewing emotional stimuli (Troy et al., 2010). A previous study demonstrated that deficits in experimentally measured CR ability are manifested in individuals with mild to moderate symptoms of depression (Zhang et al., 2016), patients in depressive episodes (Compare et al., 2014; Wang et al., 2014; Smoski et al., 2015; Wang et al., 2015), and patients in remission from depression (Ehring et al., 2008), and they can be predictive of depressive symptoms after treatment (Radkovsky et al., 2014).

One other issue of concern for CR ability is that most previous CR tasks required the subjects to generate new CR strategies of emotional stimuli under guidance rather than spontaneously (Khodadadifar et al., 2022), making it impossible to directly measure an individual’s spontaneous tendency to produce and maintain a CR strategy. According to the recent empirical literature, CR ability can be operationalized as either RE or reappraisal inventiveness (RI) (Zeier et al., 2021), with RI independent of RE (Zeier et al., 2020). RI is defined as the flexibility and semantic fluency of individuals in generating new emotional appraisals in response to specific emotion-inducing scenes, which is measured with the Reappraisal Inventiveness Test (RIT) (Weber et al., 2013). Despite the well-acknowledged effectiveness of CRs, the launching of CRs is found to be more difficult due to default preferences in the decision to regulate emotions (Suri et al., 2015). The performance of the RIT task includes RIT-fluency (the number of reappraisals generated) and RIT-flexibility (the number of categories of different reappraisals), which will be transformed into RIT scores. Thus, a higher RIT score represents greater CR abilities to generate abundant and diverse strategies to regulate emotion. Studies found that a greater RI predicts lower chronic stress levels in women and depressive symptoms in men (Perchtold et al., 2017, 2019). Greater RI, especially that which generates alternative (creative) reappraisal strategies, predicts immediate, and long-lasting beneficial effects (< 10 min vs. 3 days) in transforming negative emotion into positive emotion (Wu et al., 2019). Furthermore, the reduced ability of individuals with depressive symptoms to generate a CR strategy was observed (Perchtold et al., 2017). Therefore, the RI index is necessary for objective measurement of CR ability, and the improvement in RI may be beneficial to emotional health.

Intervention studies demonstrated that individuals’ CR ability can be improved through training and could predict changes in depressive symptoms. CR training could alleviate depressive symptoms and negative emotions, improve happiness and life satisfaction in patients with depression (Berking et al., 2013; Ehret et al., 2014; Weytens et al., 2014), and decrease short- and long-term negative emotions in healthy individuals (Denny and Ochsner, 2014). Enhancement of self-reported CR frequency after CR training compared to the wait-list control condition (WLC) could reduce the depressive symptom severity of depressed patients (Berking et al., 2019). The change in CR tendency after CBT could predict a decrease in depressive symptoms in patients with depressive disorder (Forkmann et al., 2014). A meta-analysis of emotion regulation intervention in clinical populations showed improvement in emotion regulation (including CR) tendencies (Moore et al., 2022). However, studies of the antidepressant effect of CR training on cognitively vulnerable individuals with depression are still lacking. Yuan et al. (2014) proposed that the use of CR training could reduce the vulnerability of adolescents to negative emotions, whose development stage is prone to emotional disturbances. Thus, empirical evidence for the training effects of CR on cognitively vulnerable individuals is still needed.

Notably, the neural mechanism of CR training effects is still unclear. First, deficits in CR for depressed individuals are related to aberrant activities in frontal cognitive control regions, which modulate the emotion generation regions (Khodadadifar et al., 2022), and abnormalities in the structural covariance of the emotion regulation network (Wu X. et al., 2017). (1) Cognitive control regions: The dorsolateral prefrontal lobe (dlPFC) and the ventrolateral prefrontal lobe (vlPFC) are responsible for storing and choosing appropriate CR strategies, respectively (Morawetz et al., 2016). The dorsal medial prefrontal lobe (dmPFC) is mainly responsible for monitoring and reflecting changes in an emotional state, modifying the initial emotion appraisal in adaptation to current situations/goals (top-down control of emotion) (Phillips et al., 2003). (2) Emotion generation regions, the ventral medial prefrontal cortex (vmPFC), are mainly responsible for the initial appraisal of emotional stimuli and spontaneous emotional responses (Phillips et al., 2003). The amygdala plays a major role in the effective relevance (valence) of positive and negative stimuli (Fadok et al., 2018), and its volume (especially the right side) is positively associated with CR ability (Hermann et al., 2014). The functional interactions between prefrontal subregions (dlPFC/vlPFC/dmPFC) and the amygdala probably act through the vmPFC, which has direct structural connections with prefrontal subregions and with the amygdala (D’Arbeloff et al., 2018). When depressed patients regulated negative emotion using CR, lower activation of the dlPFC, the vlPFC, and the dmPFC and higher activation of the amygdala and the vmPFC were found during the downregulation of negative emotion, and higher activation of the medial prefrontal cortex (mPFC) and lower activation of the amygdala were found during the upregulation of negative emotion (Belden et al., 2015; Picó-Pérez et al., 2017; Stephanou et al., 2017; Zilverstand et al., 2017; Radke et al., 2018). In contrast, the IFG and dlPFC/dmPFC/vmPFC effective functional connectivity (FC) patterns are indicative of reappraisal effectiveness (RE) (Morawetz et al., 2017), and the hypoactivity of the IFG in patients with depression modulated by motivation disposition during CR may interfere with inhibitory IFG-dlPFC coupling (Wang et al., 2014, 2017).

Second, there were fewer evidence indicating neural abnormalities underlying the CR abilities of individuals vulnerable to depression. Previous evidence indicated strengthened dmPFC-amygdala and vmPFC-amygdala resting-state functional connectivities in stress-vulnerable individuals with high harm avoidance (HA) personality traits (Baeken et al., 2014). In healthy individuals, stronger coupling of the dmPFC-amygdala under task-induced stress showed an enhanced immune response (Muscatell et al., 2015), which may suggest stress vulnerability. Furthermore, the associations between lower left-lateralized vlPFC activation and decreased RI ability (e.g., RIT-fluency) of individuals with depressive symptoms and chronic stress were observed, supporting the deficits in reappraisal inventiveness in individuals vulnerable to depression (Papousek et al., 2017; Perchtold et al., 2017). In contrast, the inverse relationship between the functional activities of vmPFC and amygdala in stress-resilient individuals showed more effective control over emotion response (decreased versus increased activation of amygdala) when confronted with repeated task-induced stress compared to stress-vulnerable individuals (Wang et al., 2013).

In summary, this evidence may suggest abnormalities in the prefrontal–amygdala circuits for individuals cognitively vulnerable to depression, which may lead to heightened initial affect appraisal (vmPFC↑, vmPFC-amygdala coupling↓), failure to store, generate, and monitor the need for implementing CR strategies (dlPFC/vlPFC/dmPFC↓, dlPFC/vlPFC/dmPFC-amygdala coupling↑), and selection of appropriate contextual CR strategies (IFG↓, IFG-dlPFC coupling↓).

On the other hand, the frequent user of CR showed stronger downregulation of amygdala activation to negative emotion stimuli (Kanske et al., 2012), and CR in healthy individuals can attenuate the excitatory connectivity from the dlPFC to the inferior frontal gyrus (IFG) and increase the inhibitory connectivity from the IFG to the dlPFC, which supports the selection of appropriate alternative CR strategies (reinterpretations) in the IFG, and afterward, inhibition of original interpretations maintained and monitored in the dlPFC (Morawetz et al., 2016). Neurofeedback-guided CR training targeting the left vlPFC improved the frequency of CR strategy use (indexed with ERQ) as well as depression symptoms (Keller et al., 2021). Therefore, CR training may enhance CR ability by changing the functional activity/connectivity pattern of prefrontal-amygdala circuits, which then alleviates cognitive biases and thus depressive symptoms.

Researchers suggested that specific measures using lab-based tasks may be more sensitive to detect training effects (Cohen and Ochsner, 2018). Therefore, in this study, we will combine the RIT, CR training, and fMRI, as well as self-report measures (cognitive/emotion/symptoms) to address the following aims: (1) to examine whether the CR ability (reappraisal inventiveness) of the population with cognitive vulnerability to depression is abnormal; (2) to test the hypothesis that CR training alleviates depressive symptoms through the mediators of cognitive bias (e.g., interpretation bias and/or rumination bias); (3) to investigate the neural substrates (structural/functional) of prefrontal–amygdala circuits through which CR training improves the ability to generate a CR strategy; and (4) to examine the short- and/or long-term effects of CR training on reducing depression symptoms in cognitively vulnerable individuals immediately after intervention and/or 6 months to provide theoretical and practical evidence for early intervention in these populations. We postulate that CR training improves CR ability (RIT) by changing the brain activity/function connectivity of the prefrontal-amygdala circuits, thereby reducing negative cognitive biases (NCPBQ-NIB, NCPBQ-NRB, and CSQ) and improving depression symptoms (CESD) (Figure 1).

**FIGURE 1 F1:**
[figure not shown]
Antidepressant mechanism of CR training on individuals cognitively vulnerable to depression.

## Methods

Using RIT and CR training in combination with fMRI, we will explore (1) the deficits in CR ability (indexed with RIT) for the depression-vulnerable group; (2) the short- and long-term antidepressant effects of CR training on depression-vulnerable populations; (3) whether it is feasible to reduce negative cognitive biases (negative interpretation bias and/or negative rumination bias) and depressive symptoms of depression by improving reappraisal inventiveness; and (4) the changes in the prefrontal–amygdala circuit induced by CR training, including changes in the functional activation and connectivity of the regions of interest (prefrontal cortex and amygdala) before and shortly after CR training and changes in the volumes of these regions of interest (prefrontal cortex and amygdala) long after CR training (6 months later) (Figure 2).

**FIGURE 2 F2:**
[figure not shown]
The flow diagram of the current study summarizing the randomized controlled trial design, recruitment of participants, and collected measures.

### Procedure

#### The effects of cognitive reappraisal inventiveness on individuals cognitively vulnerable to depression

Individuals cognitively vulnerable to depression will be screened using the Cognitive Style Questionnaire (CSQ) developed based on the hopelessness theory and the weakest link method. The weakest link method (Abela and Sarin, 2002) will be used to screen individuals with cognitive vulnerability to depression; it showed the value in predicting changes in depression (Reilly et al., 2012). By using a group of individuals cognitively vulnerable to depression and a normal control group as research participants, we will determine, using the RIT, whether individuals cognitively vulnerable to depression have defects in CR inventiveness before training.

#### Neural mechanism of improvements in cognitive reappraisal inventiveness in individuals cognitively vulnerable to depression through cognitive reappraisal training

Using the group of individuals cognitively vulnerable to depression (divided into intervention and waiting subgroups) and the normal control group as research participants, we will conduct a 4-week (2 sessions/week) CR training program for the intervention subgroup, and before and after training, the intervention and waiting-list control subgroups will undergo fMRI to examine whether CR training can improve reappraisal inventiveness and depression symptoms by regulating the function of the prefrontal–amygdala circuit.

#### Short- and long-term antidepressant effects of cognitive reappraisal training on individuals cognitively vulnerable to depression

Through follow-up immediately after intervention or 6 months after the intervention, we will validate the hypothesis of the reduction in cognitive vulnerability to depression and depression symptoms through improvements in reappraisal inventiveness with CR training by constructing a hierarchical linear model (HLM) analysis and mediating/modulating effect analyses.

### Subjects

The study protocol is in accordance with the Declaration of Helsinki and was approved by the ethical committee of the University. All voluntary participants have to provide informed written consent before the initiation of the study procedures.

#### Group of individuals cognitively vulnerable to depression

Of the recruited healthy subjects, those with an average weakest link score plus 1 standard deviation will be assigned to the group of individuals cognitively vulnerable to depression, and whether they have affective disorders and other axis I diseases will be determined by two experienced psychiatrists using the Structured Clinical Interview for DSM Disorders (SCID).

The inclusion criteria are as follows: participants (a) with average CSQ weakest link score plus 1 standard deviation; (b) with Han ethnicity; (c) aged 18–25 years; (d) who are right-handed; (e) with normal or corrected vision; (f) who are local community residents; (g) who can understand the content of the study, are willing to participate, and are committed to completing the entire experiment; (h) have signed informed consent form.

The weakest link composite score of CSQ will be calculated as follows: (1) calculating the scores for the 3 subscales (causes, consequences, and self-worth) of CSQ; (2) standardizing the scores for the 3 subscales and converting them to standard scores, based on which the standard scores for the 3 subscales for each individual are then ranked, in which the highest of the 3 subscale scores represents the final score for each individual’s weakest link; and (3) calculating the average weakest link scores for all individuals. The score is further used to screen individuals in the cognitively vulnerable to depression group (mean score plus 1 standard derivation) or those in the not cognitively vulnerable to depression group (the mean score minus 1 standard derivation).

The exclusion criteria are as follows: participants (a) who meet the diagnostic criteria for depression or other axis diseases; (b) with a history of taking any antidepressants or antipsychotics; (c) with a history of alcohol or drug abuse or dependence; (d) with a history of central nervous system diseases, e.g., head injury or epilepsy; (f) with a history of multiple sclerosis or major physical diseases; (g) with a history of electroshock therapy; (h) with a history of mental illness in first-degree relatives; and (i) with contraindications to MRI.

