#### Normal control group

Of the recruited healthy subjects, those with an average weakest link score minus 1 standard deviation will compose the group of individuals without cognitive vulnerability to depression, i.e., the normal control group. Individuals in the normal control group will be interviewed by two experienced psychiatrists using the SCID to exclude those suffering from depression and other axis I diseases. Ultimately, the control group will comprise 30 subjects, and the control group and the intervention and waiting subgroups of the group of individuals cognitively vulnerable to depression will be homogenous in terms of demographic variables and depression symptoms.

The inclusion criteria are described as follows: participants (a) with average CSQ weakest link score minus 1 standard deviation; (b) with Han ethnicity; (c) aged 18–25 years; (d) who are right-handed; (e) who have normal or corrected vision; (f) who are local community residents; (g) who can understand the content of the study, are willing to participate, and are committed to completing the entire experiment; and (h) who signed an informed consent form.

The exclusion criteria are described as follows: participants (a) who meet the diagnostic criteria for depression or other axis diseases; (b) history of taking any antidepressants or antipsychotics; (c) history of alcohol or drug abuse or dependence; (d) history of central nervous system diseases, e.g., head injury or epilepsy; (e) history of multiple sclerosis or major physical diseases; (f) history of electroshock therapy; (g) history of mental illness in first-degree relatives; and (h) contraindications to MRI.

Sample size calculation: An *a priori* power analysis found that a sample size of 75 participants per group (*N* = 150) would be sufficient with a medium effect size (Cohen’s d = 0.0.39) and 65% power (computed with G*power 3.1). These estimates were based on previous research examining changes in HRSD/BDI-II scores before and after CR training when compared to the waiting-list control condition (Berking et al., 2019). Since the sample size projection considered an anticipated 20% dropout rate, the target sample size was 188 patients.

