### Statistical analysis

#### Behavioral and self-report data

##### Intervention effect analysis

A 3 (group: CR = cognitively vulnerable intervention subgroup; WC = cognitively vulnerable waiting-list control subgroup; NC = normal control group) × 3 (time point: T_0_ = pretraining, T_1_ = post-training, T_2_ = 6-month follow-up) mixed design will be adopted. Using the HLM analysis, as well as mediating/modulating effect analyses, we will investigate (1) hypothesis 1, whether the changes in negative cognitive biases and depressive symptoms across time 1 and time 2 differ significantly among groups and (2) hypothesis 2, whether the changes in negative cognitive bias (negative interpretation bias and/or negative rumination bias) pre- and post-training could predict depression symptoms at T_1_ and/or T_2_.

To test hypothesis 1, we will conduct an HLM analysis with time (0 = pretraining; 1 = post-training), group (0 = CR; 1 = WC; 2 = NC), and the interaction between time and group as predictor variables and the with CESD score as the outcome variable. To test hypothesis 2, we will conduct mediating/modulating effect analyses among CR ability (RIT) and tendency (ERQ), negative cognitive bias (NCPBQ), cognitive vulnerability (CSQ), and depressive symptoms (CESD) at T_1_ and/or T_2_. The HLM and mediating/modulating effect analyses will be conducted in SPSS (Statistical Product and Service Solutions) software version 22.0 (SPSS, Inc., Chicago, IL, United States) combined with the PROCESS Macro (Hayes, 2012).

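### The mediation models for hypothesis 2 sit in a three-group design without an arm term, a normal-control term or a restriction to the randomised participants, so selection from opposite CSQ tails can inflate a RIT–bias–CESD path

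*Protocol article*

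**What the plan says.** **Selection.** Under the heading on the cognitively vulnerable group, the CSQ weakest-link score is "used to screen individuals in the cognitively vulnerable to depression group (mean score plus 1 standard derivation) or those in the not cognitively vulnerable" group. The Normal control group section confirms the lower cut-off: "those with an average weakest link score minus 1 standard deviation will compose the group of individuals without cognitive vulnerability to depression". It adds that "the control group will comprise 30 subjects" and that they and the two vulnerable subgroups "will be homogenous in terms of demographic variables and depression symptoms".

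**Randomisation.** Only the vulnerable group is divided into intervention and waiting-list subgroups, with 1:1 allocation. The sample size paragraph gives "a sample size of 75 participants per group", N = 150, and a target of 188 after dropout.

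**Analysis.** Intervention effect analysis opens with "A 3 (group: CR = cognitively vulnerable intervention subgroup; WC = cognitively vulnerable waiting-list control subgroup; NC = normal control group", crossed with three time points, and places both the HLM and the mediation/moderation analyses in that design. For hypothesis 2 it says "we will conduct mediating/modulating effect analyses among CR ability (RIT) and tendency (ERQ), negative cognitive bias (NCPBQ), cognitive vulnerability (CSQ" and CESD at T1 and/or T2 are to be related. No analysis set, treatment variable or group adjustment is given for these models. The same section first words hypothesis 2 differently, as the pre-to-post change in bias predicting CESD.

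**The concern.** Aim 2 asks whether training lowers depressive symptoms through cognitive bias. NC carry no information on that, since they are neither randomised nor trained. They do differ from the other two groups on CSQ by construction, with the middle of the distribution left out.

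In a pooled sample most of the CSQ variance is that gap. Any two variables that each correlate with CSQ will then correlate with each other across it. A path from RIT to bias to CESD at T1 or T2 could therefore be read as support for the training mechanism when it only reflects that vulnerable and non-vulnerable people differ.

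**Working it through.** **1. The plan's own figures.** No figure is given for the mediation models. The group sizes come from the sample size paragraph ("medium effect size (Cohen’s d = 0.0.39) and 65% power", read as d = 0.39). With two-sided alpha 0.05 (assumed), power = Φ(0.39 × √(75/2) − 1.96) = Φ(0.428) = 66.6%, or 66.0% with the noncentral t. Both are close to the stated 65%. Dropout: 150/0.80 = 187.5, so 188. These figures reproduce and are not affected by this point.

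**2. How much CSQ variance is the selection gap.** Assume a normal score, 150 vulnerable completers and 30 NC.
- Mean beyond 1 SD: φ(1)/(1 − Φ(1)) = 1.525. Variance within a tail: 1 + 1.525 − 1.525² = 0.199.
- Between-tail variance: (150/180)(30/180)(2 × 1.525)² = 1.292.
- Share: 1.292/(1.292 + 0.199) = 87% (85% with 188 + 30).

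**3. Effect on one correlation.** For population correlation r with CSQ and sample CSQ variance s², the sample correlation is r·s/√(1 − r² + r²s²). At r = 0.30:
- pooled (s² = 1.491): 0.36
- vulnerable tail only (s² = 0.199): 0.14

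**4. Simulation A: a true bias–symptom link, no training effect.** RIT and negative interpretation bias (NIB) are related only through CSQ. CESD correlates 0.395 with NIB, a value borrowed from the NCPBQ criterion coefficient against another depression scale. The path counts as found when RIT→NIB and NIB→CESD both have p < 0.05. Assumed CSQ correlations are 0.2–0.4 (RIT) and 0.4–0.6 (NIB).
- Three groups pooled: about 33–99% of trials.
- CR + WC only: about 6–11%.

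**5. Simulation B: RIT, bias and CESD linked only through CSQ, no training effect.** There are 75 + 75 + 30 participants, T0–T1 reliability is 0.7, and both paths must be significant in the hypothesised direction.

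| Assumed CSQ correlation (RIT/bias/CESD) | Pooled | Pooled, NC matched on T0 CESD | Unselected sample of 180 |
|---|---|---|---|
| 0/0/0 | 0.1% | – | – |
| 0.1/0.3/0.3 | 3.7% | – | – |
| 0.2/0.4/0.3 | 19.0% | 5.0% | 6.2% |
| 0.3/0.5/0.4 | 74.4% | 25.9% | 37.0% |
| 0.4/0.6/0.5 | 99.3% | 67.1% | 85.6% |

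In the 0.3/0.5/0.4 row, the unmatched rate of 74.4% falls to:
- 0.5% with an NC indicator
- 0.2% with CSQ adjusted
- 0.4% with the vulnerable arms only
- 0.2% with randomised arm as the independent variable in CR + WC

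Across all scenarios these four alternatives stay at or below 1.8%.

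**6. Two variants.**
- Change in bias predicting T1 CESD in the hypothesised direction: 2.1–2.9% in every scenario, so no inflation.
- Group coded 0/1/2 and used as a numeric predictor, without symptom matching: 0.0% in the direction favouring training, but 12.8–90.3% in the opposite direction whenever CSQ links exist.

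**The case against.** Several stronger readings are tempting, and the protocol does not support them.

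- **That the plan prescribes pooling.** It does not. Pooling is the natural reading of a three-group design with no exclusion, but the Procedure section introduces the mediation analyses under a heading about vulnerable individuals and gives NC a specific role in the pre-training RIT comparison. An analysis set can also be left to a fuller plan. What stands is that the stated design puts NC in and no sentence takes them out.
- **That recruitment alone creates the links.** It does not. With no CSQ correlations the rate is 0.1%; with RIT unrelated to CSQ (0/0.5/0.4) it is 2.4%. An unselected sample already shows confounding by vulnerability, and tail selection amplifies it.
- **That hypothesis 2 as a whole is compromised.** The change-score wording is not inflated. Only the models of T1/T2 levels are exposed.
- **That any group variable carries the gap in, or that listing CSQ makes matters worse.** A separate NC indicator removes the artefact, and so does adjusting for CSQ. The protocol specifies neither, however, and it lists CSQ among the biases that training should reduce, so its use as a covariate cannot be presumed.
- **That the imaging path models share the problem.** Scans before and after training are named for CR and WC only.

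The intended symptom homogeneity weakens the artefact without removing it: in simulation, CESD differs again by T1 (gap 0.31–0.62 SD). The Limitations section calls the bias measures exploratory, which lowers the stakes. Against that, aim 2 is worded as a hypothesis test and the Conclusion expects evidence of mediation.

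**Conclusion.** The concern holds in conditional form. If the T1/T2 level models are run on CR, WC and NC together with no group or CSQ term, a RIT–bias–CESD path can appear with no training effect. The rate is about 33–99% against about 6–11% in CR + WC only under simulation A, and about 4–67% with weaker links or symptom matching under simulation B. All these rates rest on correlations with CSQ that the protocol does not give, on a normal score and on 150 + 30 participants. They show how far the result could be driven by selection and do not forecast what this trial will find. Severity is moderate: the primary CESD comparison and the sample size are untouched.

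**What to change.** In Intervention effect analysis, state that:

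1. mediation of the training effect uses only the randomised CR and WC participants, with arm as the independent variable and baseline values adjusted;
2. NC serve the T0 RIT comparison and as a descriptive reference;
3. any model that includes NC carries a separate NC indicator, not a numeric 0/1/2 code, and is labelled associational.

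Naming arm as the independent variable matters as much as the restriction. A model among measured variables within CR + WC still would not test whether training works through bias.

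The cost is a few sentences and the loss of the 30 NC from these models (30/180 = 17%). Those participants carry no information on the randomised contrast.
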